# Efficacy of different load intensity and time-under-tension calf loading protocols for Achilles tendinopathy (the LOADIT trial): protocol for a randomised pilot study

**DOI:** 10.1186/s40814-020-00639-5

**Published:** 2020-07-13

**Keywords:** Achilles tendinopathy, Rehabilitation, Load intensity, Time-under-tension, Telerehabilitation

## Abstract

**Background:**

Modifying variables in exercise prescription can produce specific effects on Achilles tendinopathy outcomes. This study aims to determine the feasibility of conducting an adequately powered randomised trial in the future to assess the efficacy of different load intensity and time-under-tension exercise parameters for improving pain and function in individuals with persistent midportion Achilles tendinopathy.

**Methods:**

The trial is designed as prospective, four-armed feasibility and randomised pilot trial with 3 months follow-up. Interventions will be provided in a gym setting. The investigator, who will be blind to the allocation of participants, will conduct all pre- and post-intervention assessments. Forty-eight male participants with Achilles tendinopathy will be recruited from the community. We will use a 2 × 2 factorial design with factors of load intensity (six or eighteen repetitions maximum) and time-under-tension (two or six second repetitions). Participants will be randomised into one of the testing groups: six RM with two second repetitions, six RM with six second repetitions, eighteen RM with two second repetitions or eighteen RM with six second repetitions. Trial feasibility will be indicated by the rate of conversion, recruitment and retention, adherence to the interventions by participants, the utility of videoconferencing mode for weekly exercise supervision, incidence of adverse events, and feasibility of future economic evaluation. The secondary clinical outcomes will assess pain and disability, participant impression of change, satisfaction, health-related quality of life, physical activity, work absenteeism, psychological measures at baseline, 6 and 12 weeks, and plantarflexor contractile dysfunction (torque, rate of force development and muscle force steadiness) at baseline and 12 weeks. These clinical outcomes are primarily measured to provide information regarding potential treatment effects and trends.

**Discussion:**

The proposed study and follow-up powered randomised trial will be a first step towards determining exercise dose parameters that may optimise outcomes for Achilles tendinopathy. We have chosen to focus on load intensity and time-under-tension, as these parameters are important for tendon adaptation. This work has the potential to lead to more effective exercise loading interventions for Achilles tendinopathy.

**Trial registration:**

Australian New Zealand Clinical Trials Registry, ACTRN12618001315202. Registered retrospectively on August 6th, 2018.

## Background

Achilles tendinopathy is an overuse injury characterised by localised Achilles tendon load-related pain and dysfunction. This condition is often associated with a reduced ability to walk and run, which has consequential effects on general health and wellbeing [1, 2]. Achilles tendinopathy is estimated to account for up to 18% of all running injuries [3] and has an estimated cumulative lifetime prevalence of 6% in the general population [4]. The aetiology of tendinopathy is multifactorial [5], one major factor being the imbalance between load demands placed on the tendon and its ability to remodel [6]. Other factors influencing the capacity of the tendon to remodel, and thereby increase the risk of tendinopathy, include older age, genetic profile, and metabolic factors such as elevated cholesterol or diabetes. The pain mechanisms in tendinopathy are unknown and many potential structural (e.g. neurovascular ingrowth) and biochemical (e.g. changes in metabolites or cytokines) mechanisms may contribute [7].

Clinical practice guidelines, informed by systematic reviews [8, 9], recommend calf muscle exercise as a first-line treatment for Achilles tendinopathy [10]. Eccentric calf muscle loading, as originally described by Alfredson, has been—and continues to be—a popular conservative intervention for Achilles tendinopathy [11]. The intervention involves progressive, heavy isotonic exercise; only the eccentric phase is performed. Other popular isotonic resistance loading programs include the Silbernagel combined and heavy slow resistance programs [12, 13]. The Silbernagel combined program [14] involves progression from eccentric-concentric to eccentric loading, and finally to faster or plyometric type eccentric-concentric loading. Exercise is performed once daily, rather than twice as with Alfredson eccentric loading. The heavy slow resistance program [13] involves high load, progressive gym-based loading for the calf muscles performed three times per week. Comparing the efficacy of these pragmatic protocols, there is currently insufficient evidence to conclude that there is an optimal exercise protocol for Achilles tendinopathy [8, 13, 15].

The difficulty in comparing existing exercise programs for Achilles tendinopathy is that several exercise parameters vary—such as volume (number of repetitions or sets performed), load intensity (e.g. % one repetition maximum), and frequency (number of exercises performed per day)—or they are incompletely reported. Consequently, determining the dose parameters that confer the greatest benefit is not possible. For example, Beyer et al. [13] compare eccentric training and heavy slow resistance, though the latter involved lower volume and higher load intensity. Therefore, there is a need to evaluate the efficacy of calf loading exercise with varying dose parameters in people with Achilles tendinopathy.

Several variables can be modified in exercise prescription to produce specific effects on the musculotendinous system and, potentially, Achilles tendinopathy outcomes. Some modifiable variables include load intensity, time-under-tension, speed of contraction, rest between sets and frequency of exercise sessions and position of the limb. It is well established that the tendon is a mechanoresponsive tissue, and that the key driver for tendon adaptation appears to be tissue strain [16]. Given tendon tissue strain is proportional to tendon load and the amount of time this load is applied within a specific contraction (time-under-tension), it follows that these parameters will determine strain and, hence, tendon adaptation [16]. A recent systematic review of loading protocols that result in tendon adaption concluded that load intensity is the key determinant of tendon tissue adaptation to load; the type of contraction—for example, eccentric versus concentric—did not influence adaptation [17]. Although time-under-tension and load intensity are known to have specific effects on tendon adaptation, the influence of these parameters on clinical outcomes in Achilles tendinopathy is unknown. This makes examining the efficacy of load intensity and time-under-tension on Achilles tendinopathy outcomes a logical first step.

### Aims

This study aims to assess the feasibility of a future definitive randomised trial to examine the efficacy of different LOAD-intensity and time-under-tension (LOADIT) exercise parameters for Achilles tendinopathy. The primary objective is to assess the feasibility of study processes, including (i) rate of participant recruitment, conversion, and retention; (ii) ability to perform the interventions per protocol (adequate exercise fidelity and adherence based on weekly assessment via videoconferencing mode); (iii) incidence and type of adverse events; (iv) feasibility of future economic evaluation; and (v) acceptability of telerehabilitation videoconference sessions. The secondary objective is to explore trends in treatment effects and variability—in pain and disability, participant perception of change, satisfaction, health-related quality of life, physical activity, work absenteeism, psychological measures, and plantar flexion contractile dysfunction—between the groups at 6 and 12 weeks. These time points have been selected based on evidence that exercise effect should be maximised at 12 weeks [18].

## Methods

### Trial design

LOADIT is a four-arm, factorial randomised pilot study with a nested qualitative study. The factorial design is a 2 × 2: the two factors are load intensity and time-under-tension, and each has two levels (higher versus lower). Outcome assessment will occur at baseline, 6 and 12 weeks (Fig. 1). The study protocol has been reported using the Standard Protocol Items: Recommendations for Interventions (SPIRIT) statement guidelines [19] and the publication associated with the trial’s findings will be reported in accordance with the CONSORT extension for randomised pilot and feasibility trials. The protocol has been registered at the Australian New Zealand Clinical Trials Registry, ACTRN 12618001315202.

**Fig. 1 Fig1:**
[figure not shown]
Trial profile. HL: High Load; HT: High time-under-tension; LL: Low load; LT: Low time-under-tension; VISA-A: Victorian Institute of Sports Assessment–Achilles; EQ-5D-5L: Health-related quality of life; WPAI: Work Productivity and Activity Impairment; PGIC: Patient Global Impression of Change; PCS: Pain Catastrophising Scale; MVIC: Maximal Voluntary Isometric Contraction; FM10%: Force Match at 10%; RFD: Rate of Force Development; RM: Repetition Maximum

### Participant recruitment and eligibility criteria

Participants will be recruited via social media (i.e. Facebook, Twitter), and by posting study information on appropriate websites (e.g. running clubs and forums), at local community centres, senior citizen centres and sports clubs. Health professionals in Melbourne that manage Achilles tendinopathy will be asked to refer potentially eligible participants. The recruitment window is anticipated to be 6 to 8 months.

Respondents will be initially screened via telephone or email by researchers. Potentially eligible participants that satisfy the selection criteria will be provided with study information electronically and given at least 48 h to decide whether they would like to proceed.

### Inclusion criteria

Participants must meet the following criteria:
(i)Male aged 18 to 70 years.(ii)Have a history of Achilles tendon pain for 12 weeks or more.(iii)Current midportion Achilles tendinopathy in one or both lower limbs, as determined by the satisfaction of all of the following criteria (based on current recommendations [20]); (a) insidious onset of pain 2 to 6 cm above the Achilles tendon insertion; (b) pain with or after weight-bearing activities, which is worse in the morning or upon weight-bearing after a period of rest; (c) ultrasound imaging consistent with Achilles tendinopathy (anteroposterior thickness and/or hypoechoic regions within the midportion of the Achilles tendon).(iv)A score of ≤75 on the Victorian Institute of Sports Assessment—Achilles questionnaire (VISA-A).(v)Willing to attempt to access a gym three times per week to perform the exercise interventions.(vi)Willing to abstain from treatments other than the study interventions for Achilles tendon pain during the study period.(vii)Competent in both written and spoken English, and able to provide informed written consent.

### Exclusion criteria

Potential participants will be excluded if any of the following criteria are present:
(i)Previous Achilles tendon rupture or surgery in symptomatic lower limb(s).(ii)Other diagnosis of Achilles tendon pain that is not midportion Achilles tendinopathy, such as impingement syndrome, insertional Achilles tendinosis, or Achilles paratenonitis.(iii)Inflammatory arthritis, such as rheumatoid arthritis or ankylosing spondylitis.(iv)Metabolic and endocrine disorders, such as type I or II diabetes.(v)Neurological disorders affecting the lower limb, such as multiple sclerosis.(vi)Use of fluoroquinolone antibiotics within the previous 2 years.(vii)Current or recent (i.e. within the last 3 months) strength exercise treatment for Achilles tendon pain.(viii)Injection of pharmaceutical agent for Achilles tendon pain in the last 3 months.(ix)Injury of lower limb(s) or back that may interfere with the execution of exercise interventions in the study, such as fractures.

### Randomisation

Participants will be randomised to receive one of four exercise interventions. The first two arms involve lower load intensity, where participants will perform four sets of eighteen repetitions per set prior to failure (i.e. inability to do another full repetition) with either high or low time-under-tension. The second two arms involve higher load intensity, where participants will perform four sets of six repetitions per set prior to failure with high or low time-under-tension. Time-under-tension in this context refers to how long the calf muscle-tendon unit is under load. This will be exactly 6 s (3 s concentric phase, 3 s eccentric phase) in the high time-under-tension group and 2 s (1 s concentric phase, 1 s eccentric phase) in the low.

Permuted blocks of variable and undisclosed block sizes (four, eight and twelve) will be used to randomise participants to a treatment group. The allocation sequence will be computer generated and entered into sealed opaque envelopes by a researcher at a remote location who is not directly involved with trial recruitment.

### Blinding

Due to the nature of the interventions, participants and clinicians providing care will be aware of treatment allocation. Participants will be told that researchers are testing four different exercise protocols and that there is uncertainty about which is more effective. Administered and collected outcome measures will be done by a single investigator, who will be blind to treatment allocation. Research staff entering and analysing data collected in a coded data file will also be blind to allocation and uninvolved in any interventions.

### Screening

Those wishing to participate will be scheduled to attend a baseline assessment at Monash University in Melbourne, Australia, where the investigator (FH)—a qualified physiotherapist trained in performing Achilles tendon ultrasound imaging—will assess eligibility, perform baseline screening and enrol eligible participants into the study. Included participants will then be allocated to a treatment group by two trained clinical investigators, who will administer the intervention and deliver the exercise education.

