### Sample size estimation

A formal sample size calculation was not performed, as this is a feasibility study and not subjected to hypothesis testing. Instead, we made a pragmatic decision that we would be able to achieve our secondary aim by recruiting forty-eight participants to be randomised into one of four factorial arms (*n* = 12 per trial arm as a rule of thumb recommended by Julious [44]).

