## Trial Status

The trial commenced in July 2018; recruitment for the study is ongoing. The trial is funded to run up to 2020.

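### The unblinded clinicians who treat also make the allocation, so the order and timing of assignments stay within reach of people who can partly anticipate them; the block sizes called undisclosed are printed

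*Protocol article*

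**What the plan says.** All places are in the protocol article.

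- **Sequence (Randomisation).** The list is computer generated: "Permuted blocks of variable and undisclosed block sizes (four, eight and twelve) will be used to randomise participants to a treatment group". The allocations are "entered into sealed opaque envelopes by a researcher at a remote location who is not directly involved with trial recruitment".
- **Enrolment (Screening).** One investigator "will assess eligibility, perform baseline screening and enrol eligible participants into the study".
- **Allocation (Screening).** The next step passes to other people: "Included participants will then be allocated to a treatment group by two trained clinical investigators, who will administer the intervention".
- **Blinding (Blinding).** For treatment, "participants and clinicians providing care will be aware of treatment allocation". For outcomes, "Administered and collected outcome measures will be done by a single investigator, who will be blind to treatment allocation". The Abstract says that the investigator doing all assessments before and after the intervention is blind, which indicates that the enrolling investigator and the blinded assessor are the same person.
- **Size (Sample size estimation).** The plan is "recruiting forty-eight participants to be randomised into one of four factorial arms", 12 per arm.
- **Status (Trial Status).** The trial began in July 2018 and "recruitment for the study is ongoing"; the article is dated July 2020.

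The article does not say who opens the envelopes, whether they are numbered, or whether each clinician knows the other's allocations.

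**The concern.** Remote preparation of envelopes protects the sequence until someone has to use it. Here the people who use it are the two clinicians who treat, and in an open trial they accumulate knowledge of which arms have been filled. Permuted blocks pull the arms back into balance, so that knowledge says something about the next arm. Someone who both anticipates the next arm and controls when an allocation is drawn could influence which participant receives it.

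The arms differ widely in burden: Table 1 gives a total contraction time of 96 s in one arm and 864 s in another. Success criteria (ii) and (iii), on sessions completed and on fidelity, are judged within each group at 66%. With 12 per arm, one participant carries 1/12 = 8.3% of an arm's average. The exploratory contrasts between groups rest on the same small arms, and the definitive trial would inherit the process tested here.

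Separately, the Randomisation section contradicts itself: sizes cannot be undisclosed once they are printed in a public article during recruitment.

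**Working it through.** **Inputs from the article.** Four arms, 12 per arm, block sizes 4, 8 and 12. Check of the plan's own figure: 4 × 12 = 48, as stated. The article gives no figure for predictability.

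**Assumptions.** The mix of block sizes is not stated. The base case takes the three sizes as equally likely and in random order; the range runs from all fours to all twelves. How much history the allocators see is also not stated, so it is varied.

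**Formula.** In a block of size 4k where arm a has already been used c_a times, the chance that arm a comes next is (k − c_a) / (4k − total used in the block). A fully informed guesser averages this over the block sizes and starting points compatible with the history, and names the most likely arm. A naive guesser names the arm used least so far and knows nothing about block sizes.

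**Check of the simulation.** With fixed blocks of four the exact answer is (1/4 + 1/3 + 1/2 + 1) / 4 = 2.083 / 4 = 52.1%. The simulation gives 52.1%.

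**Results** (48 allocations, 10,000 to 40,000 simulated trials per scenario):

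| Scenario | Correct guesses | Of 48 |
|---|---|---|
| No history seen (chance) | 25.0% | 12.0 |
| Random half of history seen, least-used-arm guess | 29.9% | 14.4 |
| Full history, sizes unknown, least-used-arm guess | 45.8% | 22.0 |
| Full history, set of sizes known, equally likely | 45.8% | 22.0 |
| Full history, actual order of sizes known | 45.8% | 22.0 |
| Full history, all blocks of 12 | 44.0% | 21.1 |
| Full history, all blocks of 8 | 46.9% | 22.5 |
| Full history, all blocks of 4 | 52.1% | 25.0 |

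In the base case one arm has a probability of at least 50% for 32% of assignments, and at least one arm can be ruled out for 15%. The next arm is certain for 3.3%, or about 1.6 of 48. If the actual order of sizes were known, 13.5% (about 6.5 of 48) would be certain, but the share of correct guesses would not change.

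**Reading.** History drives predictability: the rate goes from 25% with none, to about 30% with half, to about 46% with all. Knowledge of the block sizes leaves it at 45.8%.

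**The case against.** The strongest reply is that a guess biases a trial only if the guesser can act on it, and the article largely prevents that. A separate assessor decides eligibility and enrols before allocation. The sequence is generated remotely and sealed in opaque envelopes. This stands, and it confines the risk to the order or timing of use.

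A reader might infer more than the article supports:

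- **That the clinicians open the envelopes, or that envelope order is uncontrolled.** The article says they allocate, not how. Numbering and logs are details that a condensed article may leave to the full protocol.
- **That they know every earlier allocation.** This requires the two to share information.
- **That they choose among waiting participants.** No queue is described. Even the planned pace is 48/8 = 6 to 48/6 = 8 a month. If recruitment was still open two years after July 2018, the real pace was at most about 48/24 = 2 a month, so participants waiting together would be uncommon.
- **That they influence screening.** The recruitment section mentions only researchers in general.
- **That printing the block sizes makes the next arm guessable.** It adds no correct guesses and could touch only participants randomised after publication.

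It is also fair that this is a pilot with no hypothesis test, and that nothing in the article suggests steering took place. The objection does not remove the stated fact that unblinded treaters make the assignment.

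**Conclusion.** The point holds in a limited form. The article gives the assignment step to the two unblinded clinicians who deliver treatment, and it prints block sizes that it calls undisclosed while still recruiting. Selection at enrolment is well guarded, so the exposure is to the order or timing of allocations.

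Its size depends on what the clinicians know. With the full history shared, about 46% of assignments can be guessed (44% to 52% across block mixes); with half the history, about 30%; by chance, 25%. Certainty is rare, at about 3%. The 46% rests on two assumptions that the article does not settle: shared full history and, for the central value, equally likely block sizes. The effect on the adherence and fidelity criteria was not quantified; the 8.3% weight of one participant shows only how sensitive an arm of 12 is. The matter deserves a short amendment because the remedy is nearly free and the process is meant to be carried forward.

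**What to change.** In Randomisation and Screening, state that the remote researcher who generated the sequence keeps it and releases one allocation at a time, with a dated log. Release follows only after the blinded assessor has completed baseline testing and registered the participant. The treating clinicians receive the allocation and hold no envelopes.

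They may still guess the next arm, but they no longer control when an allocation is drawn. The order is then set by registration, which lies with an assessor who sees no allocations and so guesses at 25%. The word undisclosed should also go, since the sizes are public.

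Changing the block sizes partway through is not worthwhile: under full history, sizes of 8 and 12 alone would still allow 44.5% correct guesses.

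The cost is a short amendment, one message per participant to a researcher already in the trial, and a short wait for each allocation. No extra staff or participants are needed.

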### Baseline assessment

i.Participant characteristics and anthropometrics

Anthropometric data, including weight and height, will be collected. Researchers will use structured questionnaires to obtain demographic and injury data, including presentation of symptoms (side of injury, dominant leg, pain location, duration of symptoms, perceived cause, previous diagnosis and treatment), level of physical activity (current and ultimate goal), presence of medical conditions (medical history and surgical history) and general health. The location of Achilles pain, pain quality and intensity will be measured via the digital application (Navigate Pain, Aglance Solutions, Aalborg, Denmark) [21].

For baseline testing, the painDETECT questionnaire will be implemented to screen neuropathic pain. This is a validated patient-reported measure that identifies the presence of neuropathic pain with high sensitivity, specificity, and positive predictive value [22]. The questionnaire is scored from zero to thirty-eight: a response between zero and twelve indicates that neuropathic pain is unlikely (<15%). A score of thirteen to eighteen is equivocal, and a score of nineteen or more indicates neuropathic pain is very likely (>90%).

ii.Plantar flexion contractile function

Plantarflexor maximal voluntary isometric contraction and rate of force development

Rate of force development (RFD) and maximal voluntary isometric contraction (MVIC) will be assessed using a custom-built ankle dynamometer. These measures intend to provide important information regarding neural and mechanical adaptations to load training [23]. Participants will be seated barefoot in the dynamometer with the ankle in plantargrade and knee joint flexed to 50° to optimise activation of soleus and gastrocnemius [24].

